#### 5.2.2. Maternal Measures

##### Stress Measures

To determine stress, questionnaires administered at baseline will also be administered at hospital discharge. The final PSS-NICU scores will be compared between the intervention and control groups, and between two different time points (i.e., pre- and post-intervention).

##### Maternal Presence in the NICU

Measures of attendance and the frequency and/or time spent using maternal self-report forms will be filled out after each visit to the NICU. The mothers in both groups will be asked to enter information about the frequency and duration of their visits to the NICU. All questionnaires on maternal presence in the NICU will be collected at discharge. The final data will be the duration of maternal presence in the NICU (min) for each day of hospitalisation and the frequency of visits. 

## 6. Blinding

The nature of the present trial does not allow blinding for the included patients for either group. Physiological data analysts will be blinded after their assignment to interventions. Double blinded coding will be assured for video analysis; two trained blinded coders will perform the GMs analysis through silent videos. Cognitive and linguistic tests will be administered and coded blindly. 

## 7. Potential Confounds

A limitation of the study is the potential contamination between the intervention and control groups. Whenever possible, the mothers of the two groups will not simultaneously be present in the same hospital room.

## 8. Statistical Analyses

### 8.1. Primary Outcome

The modulation of vagal activity will be tracked as a function of time during the interaction between the infants and mothers, by calculating the LF and HF power of the HRV and investigating respiratory sinus arrhythmia. The acquired autonomic signals (e.g., ECG, PPG, and breath signal) will be analysed to evaluate the differences between the physiological responses related to the different experimental groups. Standard analysis techniques that involve the extraction of parameters in the time and frequency domain will be applied in the first instance. 

Intra-group analysis (considering the control group and the intervention group separately) will be performed with the Friedman test by comparing the values of HRV parameters extracted from the three sessions (pre, yes and post). Post-hoc correction (Bonferroni method) will be applied. Inter-group analysis (between the control group and the intervention group) will be performed with the Kruskal–Wallis test by comparing HRV parameters of the first five-minute window of each session (pre, yes and post) between the two groups. Finally, innovative methods of analysis aimed at applying the chaos theory to physiological signals will be used to study the complexity of autonomic dynamics and the nonlinear coupling between the autonomic subsystems. These nonlinear analysis techniques will be applied both univariate (using a single signal, preferably HRV) and multivariate (e.g., considering HRV and pulse rate variability at the same time) domains.

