### 3.7. Sample Size and Power Analysis

The main outcome measures for the primary outcome will be the low-frequency (LF) and high-frequency (HF) power of the HRV measure. We expect the baseline measurement mean value (±standard deviation) of LF and HF power for preterm infants to be 31 ± 4.9 Hz and 15 ± 2.6 Hz, respectively [58]. We assume that the treatment in the experimental population is effective if the mean values of LF and HF power reach 25 ± 4.9 and 17 ± 2.4 Hz, respectively. 

With an alpha setting at 0.025 and beta setting at 0.80, it is necessary to enroll 29 patients per group. Assuming a 20% loss, we aim to enroll at least 80 patients total (40 per group).

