### 3.8. Randomisation

A centralised patient randomisation will be performed using a secure, web-based randomisation system, through which the study investigator of each centre can register new patients and obtain the treatment arm assignment.

A block allocation sequence with variable block sizes (block size 2–4), stratified by GA and gender, will be generated using Stata statistical software (StataCorp, College Station, TX, USA) with the “ralloc” command. In case of twins, randomisation will be conducted at the level of the family (i.e., twins will be randomised to the same group). The allocation sequence will be concealed from the investigators.

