## 4. Measures

### 4.1. Baseline Measures

#### 4.1.1. Infant’s Measures

As a physiological assessment, electrocardiogram (ECG) recordings will be collected during a 20-min baseline period, in the absence of the mothers, at the same hour as that of the intervention. We will also use a qualitative assessment of general movements (GMs) to assess behaviour. A video of the baby’s general movements will be collected in the baseline period. The video coding will be performed on blinded videos by two independent researchers.

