## 5. Outcome Measures

### 5.1. Primary Outcome Measure

#### Physiological Level

During the interventions, time and frequency analysis of HRV will be applied to the following parameters: LFpower (power in the LF band), HFpower (power in the HF band), LFnu (normalised power in the LF band [LF power/(LFpower + HFpower)]); HFnu (normalised power in the HF band [HF power/(LFpower + HFpower)]); LF% (percentage power in the LF band [LF power/total power]), HF% (percentage power in the HF band [HF power/total power]), and LF/HF (ratio between LF power and HF power). The change from baseline will be calculated across the three conditions (i.e., singing, speaking, and control).

HRV will be measured through the acquisition of the ECG signal, via electrodes placed on the infant’s chest by routine medical devices. Subsequently, the ECG signal will automatically be recorded by the IxTrend Software (Ixellence GmbH, Wildau, Germany). Moreover, the heart rate (beats per minute), oxygen saturation (%), and all critical events (hypoxemia, oxygen saturation <80%; bradycardia, heart rate <80 bpm) will be acquired during the different conditions using the relevant medical apparatus. 

The physiological level is strictly dependent on the infant’s behavioural state (i.e., quiet, active, indeterminate, awake, or crying), which will be assessed offline from the video-recorded sessions by blinded coders, according to the Prechtl scale [8]. Measures of physiological parameters will be collected over the intervention period, as well as 20 min before and after the mother’s intervention.

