### 8.2. Secondary Outcomes

To assess the effect of EVC on the neurobehavioral and developmental outcomes of newborns, as well as on maternal stress and presence in the NICU, the values for the different scales and questionnaires will be compared (at the time points specified in the Secondary Outcome Measures) between the intervention and control groups. Confounding variables will be entered in the analysis (i.e., familiar socio-economical score, gestational age at birth) to partial out any effect which they could have on the difference between the outcome measures. For continuous variables the Wilcoxon-Mann-Whitney test will be applied, while for categorical variables the chi-squared test (or Fisher’s exact test where appropriate) will be applied. 

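### Section 5.1 announces change from baseline in HRV, but the only between-arm test named in Section 8.1 compares unadjusted raw levels, and each infant's own pre value enters only within-arm tests

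*Protocol article*

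**What the plan says.** **Outcome.** Section 5.1 (Physiological Level) lists seven HRV parameters and adds: "The change from baseline will be calculated across the three conditions (i.e., singing, speaking, and control"). Section 3.7 names LF and HF power as the main measures and sizes the trial on their mean levels, expecting "LF and HF power for preterm infants to be 31 ± 4.9 Hz and 15 ± 2.6 Hz, respectively" at baseline.

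**Between-arm test.** The inter-group analysis in Section 8.1 "will be performed with the Kruskal–Wallis test by comparing HRV parameters of the first five-minute window of each session (pre, yes and post"). No covariate is named.

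**Within-arm tests.** The same section states: "Intra-group analysis (considering the control group and the intervention group separately) will be performed with the Friedman test", across the pre, yes and post values. The next sentence reads "Post-hoc correction (Bonferroni method) will be applied".

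**Design and data available.** Section 3.8 describes "A block allocation sequence with variable block sizes (block size 2–4), stratified by GA and gender". Section 4.1.1 states that "electrocardiogram (ECG) recordings will be collected during a 20-min baseline period, in the absence of the mothers", and Section 5.1 adds recordings for 20 minutes before and after each intervention. Section 2 says that HRV correlates with GA.

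**Adjustment elsewhere.** Section 8.2, for the secondary outcomes only, says: "Confounding variables will be entered in the analysis (i.e., familiar socio-economical score, gestational age at birth").

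**The concern.** The announced quantity and the named test differ. A between-arm comparison of raw levels in each window contains no change and no baseline, so the change in Section 5.1 has no between-arm test in Section 8.1. An analysis plan cannot follow both sections as written. If the choice between level and change is made after the data are seen, the primary result is open to selection.

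Three further features follow from the stated text:

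- The pre window is listed as a between-arm contrast beside yes and post. At an infant's first session it can only show chance balance between randomised arms.
- The article says GA matters for HRV, stratifies on GA and adjusts secondary outcomes for it, yet names a primary test that cannot take covariates.
- The only planned tests that use an infant's own pre value are run within each arm. A significant result in one arm and not in the other is not evidence that the arms differ.

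**Working it through.** **1. The plan's own figure (Section 3.7).** Inputs for HF: means 15 and 17, SDs 2.6 and 2.4, alpha 0.025 (read as two-sided; the article does not say), power 0.80 (printed as beta).

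- Pooled SD = √[(2.6² + 2.4²)/2] = 2.50; standardised difference = 2/2.50 = 0.80.
- n per arm = 2 × (2.241 + 0.842)² × 2.50² / 2² = 29.75, so 30 against the stated 29. This reproduces.
- LF (difference 6, SD 4.9) needs only 13 per arm, so HF drives the size.
- The calculation is a two-sample comparison of raw levels. With 40 enrolled per arm and 20% lost, 40 × 0.8 = 32 remain.

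**2. What ignoring the pre value costs.** Let r be the correlation between an infant's pre and during values. The documents give no r, so a range is shown. Relative to raw levels, the variance of the arm contrast is multiplied by 2(1 − r) for a plain change score and by 1 − r² for ANCOVA.

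HF power at 29 per arm, by power = Φ(δ / (SD·√f·√(2/n)) − 2.241), where f is the variance factor:

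| r | raw level | change score | ANCOVA | ANCOVA n per arm for 80% |
|---|---|---|---|---|
| 0.3 | 0.79 | 0.63 | 0.83 | 28 |
| 0.5 | 0.79 | 0.79 | 0.90 | 23 |
| 0.7 | 0.79 | 0.95 | 0.98 | 16 |

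At 32 per arm, simulation of the Kruskal–Wallis test on the yes values gives about 78–80%, whatever r is. ANCOVA on the pre value gives about 83–85% (r = 0.3), 91–93% (r = 0.5) and 98% (r = 0.7). The ranges cover simulation and t-based or normal calculation. For LF, power already exceeds 99% unadjusted.

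**3. What the separate Friedman tests can show.** Suppose both arms have the same true response during the session, and let p be the chance that Friedman is significant in one arm. Exactly one arm is then significant with probability 2p(1 − p), which is at most 0.50 (at p = 0.5). Simulation with 32 per arm, within-infant correlation 0.5 and test level 0.05:

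| Common response (SD) | Exactly one arm significant |
|---|---|
| 0 | about 9% |
| 0.2 | about 26% |
| 0.3 | about 40% |
| 0.4 | about 50% |
| 0.7 | about 13% |
| 0.9 | about 1% |

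The risk is large only for moderate responses, but there it is close to a coin toss although the arms do not differ at all.

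**The case against.** **The test is valid.** An unadjusted rank test of randomised arms keeps its type I error. A reader might infer that leaving out baseline and strata biases the comparison. It does not: chance imbalance is part of the sampling variation that the p-value covers. This stands, and it limits the point to precision and alignment.

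**Section 5.1 is not a clean definition.** Section 3.7 names LF and HF power and sizes on levels; Section 5.1 only says that change will be calculated. This stands too. The sections are unreconciled, rather than one clearly violating the other.

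**The gain may be small.** Section 5.1 ties physiology closely to behavioural state, so a low r is plausible, and at r = 0.3 ANCOVA adds only about four percentage points under normal theory at 29 per arm (0.79 to 0.83). For LF there is nothing material to gain. This is fair, but the adjustment does not require r to be high and uses data already collected.

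**Nobody says that discordant Friedman results will be read as an effect.** Correct. A between-arm test is planned alongside them, so the article does not support a claim that it rests its conclusion on within-arm significance. What remains is that these are the only tests that use the pre value, and their role is not stated.

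**Covariates are often left to the analysis plan.** This holds for centre and postmenstrual age, whose absence from a condensed article is no error. A reader might also infer harm from allocation not being stratified by centre, but the article reports no centre effect on HRV. The point here rests on the test that is stated.

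**Conclusion.** The concern holds as a mismatch between Sections 5.1 and 8.1 and as an avoidable loss of precision. The named between-arm test does not address the change from baseline, and the pre value is used only in tests that do not compare the arms. For HF, Kruskal–Wallis sits at about the planned power, while baseline adjustment would raise it by a few percentage points at r = 0.3 and to about 98% at r = 0.7. These figures rest on the Section 3.7 means and SDs, two-sided alpha 0.025, 32 evaluable infants per arm, one value per infant and an assumed r.

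Two stronger readings are not supported. The sample size is not wrong: 29 reproduces to within one infant per arm. Nor is a plain change score the natural remedy: below r = 0.5 it has less power than raw levels (0.63 against 0.79 at r = 0.3). The matter should be settled before any data are compared by arm.

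**What to change.** In Section 8.1, replace the Kruskal–Wallis comparison with one between-arm model for LF power and HF power in the yes period, log-transformed if skewed:

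- **Terms:** arm, the same infant's pre value, and the stratification factors GA and gender. Centre may be added.
- **Which baseline:** say whether it is the Section 4.1.1 recording or the 20 minutes before a session. After the first session, a pre value is measured after randomisation and could already carry an effect of EVC, so the two choices answer different questions.
- **Dependence:** a random effect or robust standard error for the six sessions per infant (three per week for two weeks, Section 3.9) and for twins, who share an arm (Section 3.8).
- **Conditions:** a stated rule for how singing and speaking enter, since Section 5.1 names three conditions and Section 8.1 compares two groups.
- **Reporting:** the adjusted arm difference with its confidence interval.

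Drop pre as an outcome contrast. Label the Friedman tests descriptive, with no between-arm inference drawn from them. Keep a rank-based ANCOVA as a sensitivity analysis, and align the wording of Section 5.1 with the model.

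The cost is wording plus slightly more analysis work. The pre recordings, GA and gender are already collected. The downside is reliance on model assumptions, which the rank-based analysis checks.

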## Abstract

Preterm infants are at risk for developing altered trajectories of cognitive, social, and linguistic competences compared to a term population. This is mainly due to medical and environmental factors, as they are exposed to an atypical auditory environment and simultaneously, long periods of early separation from their parents. The short-term effects of early vocal contact (EVC) on an infant’s early stability have been investigated. However, there is limited evidence of its impact on the infant’s autonomic nervous system maturation, as indexed by heart rate variability, and its long-term impact on infant neurodevelopment. Our multi-centric study aims to investigate the effects of EVC on a preterm infant’s physiology, neurobehaviour, and development. Eighty stable preterm infants, born at 25–32 weeks and 6 days gestational age, without specific abnormalities, will be enrolled and randomised to either an intervention or control group. The intervention group will receive EVC, where mothers will talk and sing to their infants for 10 min three times per week for 2 weeks. Mothers in the control group will be encouraged to spend the same amount of time next to the incubator and observe the infant’s behaviour through a standard cluster of indicators. Infants will be assessed at baseline; the end of the intervention; term equivalent age; and 3, 6, 12, and 24 months corrected age, with a battery of physiological, neurobehavioral, and developmental measures. Early interventions in the neonatal intensive care unit have demonstrated effects on the neurodevelopment of preterm infants, thereby lowering the negative long-term effects of an atypical auditory and interactional environment. Our proposed study will provide new insight into mother–infant early contact as a protective intervention against the sequelae of prematurity during this sensitive period of development. Early intervention, such as EVC, is intuitive and easy to implement in the daily care of preterm infants. However, its long-term effects on infant neurodevelopment and maternal sensitivity and stress are still unclear. Trial Registration: NCT04759573, retrospectively registered, 17 February 2021.

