### 3.9. Intervention

This intervention will start soon after birth, once the inclusion criteria are met, and will continue over 2 weeks during hospitalisation, minimising the effect of mother–infant separation in the NICU. In any case, participants will be excluded if they reach the inclusion criteria at more than 36 weeks of GA at test, thus when it’s presumed that they will not complete the two weeks of intervention. 

The EVC will take place in the hospital room while infants are in their individual incubators or open cribs. In the intervention group, mothers will be asked to speak and sing to their infants continuously over a 10 min period for each type of intervention (20 min in total). Mothers will be asked to talk in their native language and to sing familiar songs, while observing their infant’s reactions. The order of the two vocalisations, speaking and singing, will be reversed in the next intervention.

EVC will be performed by mothers three times per week for 2 weeks, more than 1 h after afternoon feeding. It will begin when the newborns are in an active sleep state, in calm awake state or in active awake state, but not in deep sleep or crying. 

The intervention will not begin during deep sleep state, in order to protect the infant sleep cycles and his stability [27]. The calm awake state is the most suitable for beginning early sensory interventions and interaction with the family, in stable preterm infants [70]. However, there is the need not to overwhelm the infant in this precious attentional state, where the brain expects sensory experience to grow and mature [20].

Preterm infants will be enrolled from 25 + 0 to 32 + 6 weeks of GA, following the established inclusion criteria.

Two fixed cameras will record the facial and upper torso movements of the mothers and infants. Mothers will be free to choose the content and style of their speech and singing, but will be asked to refrain from touching the infant, while maintaining eye contact with them. They will be told to place their face in front of the incubator opening so as to be as close as possible to the infant’s head. 

To improve adherence to the intervention protocol, concomitant medical procedures will not be permitted during the intervention. 

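### The only named between-group primary test uses two groups and the first five minutes of each period, so it does not match the primary measure, which is change from baseline under singing, speaking and control.

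*Protocol article*

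**What the plan says.** All references are to the protocol article.

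- **Primary measure (section 5.1, Physiological Level).** "The change from baseline will be calculated across the three conditions (i.e., singing, speaking, and control". On the recordings: "Measures of physiological parameters will be collected over the intervention period, as well as 20 min before and after" the session.
- **Session content (section 3.9).** Mothers vocalise "continuously over a 10 min period for each type of intervention (20 min in total". On sequence: "The order of the two vocalisations, speaking and singing, will be reversed in the next intervention". On frequency: "EVC will be performed by mothers three times per week for 2 weeks", which makes six sessions.
- **Between-group test (section 8.1).** Kruskal–Wallis, intervention against control, on "HRV parameters of the first five-minute window of each session (pre, yes and post) between the two groups".
- **Within-group test (section 8.1).** Friedman, in each arm separately, "comparing the values of HRV parameters extracted from the three sessions (pre, yes and post", with Bonferroni correction afterwards.
- **Session length in the abstract.** "mothers will talk and sing to their infants for 10 min three times per week for 2 weeks". This can be read as 10 min for the two vocalisations together, against 20 min in section 3.9.

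**The concern.** The measure has three conditions and is a change from baseline. The named arm comparison has two groups and takes the level in one window of each period. A statistician who followed section 8.1 literally would not produce the quantity set out in section 5.1.

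The choice of window adds to this. In the intervention arm the first five minutes show the response at the onset of whichever vocalisation came first. The second vocalisation in that session never enters the arm comparison, nor does the later part of the first.

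At stake is what the primary result means. It would be an onset response to a mixture of speaking and singing, reported under an outcome that separates them, and most of the recorded exposure would not contribute to it.

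**Working it through.** **1. Time arithmetic, section 3.9 lengths**

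- Intervention period: 10 + 10 = 20 min. Window: 5 min.
- Share of the intervention period used: 5/20 = 25%. Left out: 20 − 5 = 15 min.
- Share of the first vocalisation covered: 5/10 = 50%. Share of the second: 0/10 = 0%.
- The pre and post periods are also 20 min each, so the share used there is again 25%.

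If the abstract's 10 min is the total, the share is 5/10 = 50%. If that total were split equally (an assumption), the window would cover all of the first vocalisation and still none of the second.

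**2. Across sessions**

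- Sessions: 3 per week × 2 weeks = 6.
- With the order reversed each time, speaking comes first in 6/2 = 3 sessions and singing in 3, if all six are held and analysed.
- So the full set of first windows contains both vocalisations. If a single session were analysed, each infant would contribute only one. Section 8.1 does not say which sessions are used.

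**3. What each named test can return**

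| | Arms compared | Singing and speaking separate | Change from baseline |
|---|---|---|---|
| Section 5.1 measure | control is one of the conditions | yes | yes |
| Kruskal–Wallis (8.1) | yes | no | no: the level in each period |
| Friedman (8.1) | no | no | within one arm only |

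Neither test gives the section 5.1 quantity, and the two together do not either. A within-arm change in each arm plus a between-arm comparison of levels is not a between-arm comparison of change.

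**4. The sample size is not affected**

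Inputs from section 3.7: HF 15 (SD 2.6) against 17 (SD 2.4), alpha 0.025, power 0.80.

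- Pooled SD = √[(2.6² + 2.4²)/2] = 2.50.
- n per group = 2 × [2.50 × (2.241 + 0.842)/2]² = 29.75, so 30 with a two-sided alpha, against 29 stated. The difference is rounding; power at 29 is 0.789.
- LF (difference 6, SD 4.9) needs 13, so HF sets the size.

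The calculation contains no window, session or condition term, so it neither supports nor undermines the choice of window.

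**5. Possible precision gain (assumption-based)**

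The article gives no within-infant correlation. For k values with common correlation r, the variance of their mean relative to one value is (1 + (k − 1)r)/k.

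- Four windows in a period, r = 0.4, 0.6, 0.8 (assumed): 0.55, 0.70, 0.85, a reduction of 45%, 30%, 15%.
- Six sessions, r = 0.3, 0.5, 0.7 (assumed): 0.417, 0.583, 0.75, a reduction of 58%, 42%, 25%.

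These figures describe the level in a period, not the change score. They turn into power only if the effect is similar across the windows averaged.

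**The case against.** **The reversal of order rescues the contrast.** A reader might infer that a first-window rule makes the singing/speaking/control contrast impossible. It does not: over six sessions each vocalisation comes first about three times, and the sessions could be split by type. This stands. The contrast is missing because the test is written for two groups and no split is specified, not because the window lasts five minutes.

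**Section 5.1 says the change will be calculated, not that the three-way contrast is the hypothesis test.** This is fair: sections 1.5 and 3.7 frame the question as EVC against control. It supports keeping EVC versus control as the main test. It does not explain why that test leaves out both the change from baseline and the second vocalisation.

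**The window limit applies to one analysis only, and equally to both arms.** True. The Friedman test carries no such limit, section 8.1 also promises to follow vagal activity over time, and a window of the same length and position in each arm does not bias the randomised comparison. The issue is what is measured and how much of it, not bias.

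**Repeated sessions.** A reader might infer that six sessions per infant must be either discarded or pooled as independent, with an inflated type I error. The article states neither. Averaging to one value per infant fits both named tests, and an article may leave that detail to the full plan. No claim about type I error is made here.

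**Lost power.** A reader might infer that the window costs planned power. The SDs in section 3.7 come from a cited study that is not at hand; if they reflect a similarly short window, planned power is unchanged.

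**Conclusion.** The mismatch between sections 5.1 and 8.1 is real and should be corrected. Followed as written, the between-group test does not use change from baseline, does not separate singing from speaking, and uses 25% of the intervention period (50% if the abstract's 10 min is the total). Within a session it sees only the vocalisation that came first; across sessions it mixes the two.

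These points rest only on the stated lengths, order and tests. The count of three sessions per vocalisation assumes that all six are held and analysed. The variance reductions of 15–45% for windows and 25–58% for sessions rest on assumed correlations and show only what might be gained. The comparison is not shown to be biased, and the sample size is untouched.

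**What to change.** 1. **Reconcile the texts.** Make section 8.1 analyse the measure in section 5.1, and settle whether the abstract's 10 min and section 3.9's 20 min mean the same session.
2. **Windows.** Compute HRV in five-minute windows across both vocalisation blocks, the time-matched control periods and the pre periods.
3. **One value per infant per condition.** Average windows, then sessions, so that repeats are not treated as independent. Form the EVC value as the mean of the speaking and singing values. State which sessions count and what happens when some are missed, because the balance of order is exact only with equal numbers starting with each vocalisation.
4. **Main test.** EVC versus control on change from, or adjusted for, the pre value. Speaking versus control and singing versus control are secondary contrasts.
5. **Baseline.** Say whether it is the pre period of each session or the separate baseline recording in section 4.1.1. From the second session on, pre values are taken after EVC has begun, so a contrast against them measures the response within a session, not a cumulative shift.
6. **Keep the first-window test** as a sensitivity analysis.

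The cost is somewhat more signal processing and revised wording, with no extra infants, visits or recordings. A mixed model over all windows and sessions is an alternative, but this mismatch does not require one. Averaging could dilute an effect confined to the onset, which is a reason to keep item 6.
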